**Table 1 Tab1:**
[figure not shown]
Showing SPIRT figure for the enrolment, baseline, intervention, and assessments

### Study setting

The study is being conducted in Kingston upon Hull, UK. The participants will be identified and recruited via Hull University Teaching Hospital NHS Trust.

Recruitment began in January 2022 and will cease in May 2022 or when the sample size has been reached. The sample size was pre-specified at 35 individuals LWBLC. The sample size is based on a recent systematic review that examined the feasibility, acceptability, and potential efficacy of online supportive care for those LWBLC [40], literature regarding sample size for pilot and feasibility studies [45, 46], and clinical expertise from a senior lung oncology consultant.

### Participants and screening

The participants will be recruited through the lung cancer clinic at Hull University Teaching Hospital. The primary investigator will disseminate the recruitment information with assistance from participating site oncologists to those who meet the inclusion criteria during routine appointments. Interested participants will contact a member of the research team to obtain informed consent, provide answers to any outstanding questions, and process baseline data collection. Figure 1 illustrates a flow diagram of participant engagement.

**Fig. 1 Fig1:**
[figure not shown]
Demonstrating the flow of participants throughout the study

### Eligibility

The participants will be screened against predetermined eligibility criteria and approved for physical activity by their clinician. The participants must have received a lung cancer diagnosis or cancer of the lung (e.g. pleural mesothelioma), either non-small cell lung cancer or small cell lung cancer. In addition, the participants must be 18 years or older, able to speak and communicate in English, be willing to provide informed consent, have access to a smart device that can display the website (e.g. laptop or tablet), and have internet access.

The participants will be considered ineligible if they are under 18 years of age at the time of screening, unable to provide informed consent due to cognitive or linguistic inability, or have a physiological and/or cognitive impairment that would prevent or inhibit participation of moderate aerobic and resistance-related physical activity. In addition, the participants will be excluded if they have identified bone metastases in weight-bearing locations and/or spinal compression, which may inhibit or prevent their safe participation in unsupervised exercise.

### Intervention

#### Intervention development and adaptions

##### Early development

The original conception of the web-based platform on which ExerciseGuide was built and was developed by Vandelanotte and colleagues [47]. Previously ExerciseGuide has been adapted and used in oncological populations such as breast cancer [41, 42] and metastatic prostate cancer [39]. To ensure the adaption of ExerciseGuide for those LWBLC, an iterative adaptive process was undertaken (see Fig. 2).

**Fig. 2 Fig2:**
[figure not shown]
Overview of the process taken to adapt and create new content for ExerciseGuide UK

A systematic review was initially undertaken to appraise the current literature regarding the feasibility, acceptability, and potential efficacy of online supportive care platforms for those LWBLC [40]. Subsequently, iterative patient and public involvement (PPI) workshops were conducted with volunteers who had experience with LWBLC as a patient, carer of someone, or family member. Think Aloud interviews were conducted with seven participants LWBLC via Zoom. Positive and negative quotes pertaining to each given task were presented in tabular format (see supplemental material 1). A detailed summary of the Think Aloud interviews can be found in supplemental material 2.

##### Final adaptions

The agreed change was by a mutual consensus with the PPI members. An example of agreed change can be demonstrated within the formerly known library. The participants in the Think Aloud interviews struggled to find a location where extra information would be located and once found, believed the library looked “boring.” Therefore, agreements were reached with the PPI group and research team to change the name “Library” to “Extra Information” and apply image thumbnails to the hyperlinks to provide a more inviting and interesting page (see Fig. 3).

**Fig. 3 Fig3:**
[figure not shown]
Original (left) and revised (right) screenshots of the Extra Information page (formerly known as Library) on ExerciseGuide UK. Revisions were made based on Think Aloud interviews and agreement with the PPI group

#### Intervention description

ExerciseGuide UK consists of 18 modules released over 8 weeks. A complete list of the modules can be found in the supplementary material. The website architecture adopts a tunnelled approach, as opposed to free choice. A tunnelled approach allows users to access small batches of information over a pre-specified time and with a predetermined flow [48] opposed to immediate full access [49]. The tunnelled design and module release timings are illustrated in Fig. 4.

**Fig. 4 Fig4:**
[figure not shown]
Website flow over 8 weeks

The dashboard (shown in Fig. 5) where modules become active throughout the intervention duration. Upcoming modules will be displayed on the dashboard with a countdown until they become accessible.

**Fig. 5 Fig5:**
[figure not shown]
Illustrating an example of the dashboard

#### Website tailoring

The website will deliver computer-tailored evidence-based modules, including an 8-week exercise programme and supporting information. The content of the modules will be tailored based on individual participant characteristics through an automated computer process using IF-THEN statements. Modules will contain questions that will have a corresponding message (or feedback item) in the database. Thus, IF a participant answers one or more questions, THEN the corresponding message(s) will appear in the module. Computer tailoring has been shown to increase efficacy and safety of behaviour change and physical activity by delivering personally relevant content [50–52]. An outline of the modules containing feedback items, their tailoring properties, and the behaviour change mechanism of action is detailed in Table 2.

**Table 2 Tab2:** Illustrating the breakdown of modules, description, tailoring, and mechanisms of action

Module	Module description	Tailoring	Mechanism of action
Getting started	Introductory module to the website. Demonstrating how to use and navigate the website.	No tailoring	● Knowledge ● Self-efficacy
Physical activity programme	Provide a personally tailored physical activity programme in two sections. Section one will cover week 1 to week 3. Section two will cover week 4 to week 8. Additionally, introductory safety information is provided.	Tailoring was based on pre-set questions which covered prior physical activity and exercise experience, physical health limitations.	● Knowledge ● Self-efficacy ● Intentions
SMART goals	Provide information regarding SMART goals. Linked to the Action plan. Participants will set their own SMART goal.	Personalised introduction with messaged based on previous goal setting habits.	● Knowledge ● Goals/behavioural Regulation ● Intentions ● Motivation
Action plan	Supported by the SMART goals module, the action plan guides participants to set a personally relevant and meaning plan to achieve their SMART Goal.	Not tailored. Participants are guided to set an action plan with specific questions. Ultimately setting a personalised action plan.	● Goals/behavioural Regulation ● Intentions ● Motivation
Exercise safety	Provide safety information for those LWBLC regarding being physically active and engaging in exercise.	Further in-depth guidance is provided for specific health- and cancer-related concerns.	● Knowledge ● Self-efficacy ● Beliefs about capabilities ● Needs ● Perceived Susceptibility/vulnerability
Exercise benefits	Provide informative content surrounding benefits of physical activity for those LWBLC.	Health issues and cancer-related side effects which may be improved via physical activity and exercise.	● Knowledge ● Optimism ● Self-efficacy ● Intentions ● Motivation ● Beliefs about consequences
Motivation	Content surrounding motivation, barriers and enablers to physical activity, and habit formation.	Identify and assistive feedback on specific barriers to physical activity and exercise.	● Emotion ● Attitude towards the Behaviour ● Values ● Motivation ● Automaticity
Tracking module	Provides an opportunity for self-monitoring of exercise and healthy lifestyle behaviours and outcomes.		● General attitudes/beliefs ● Self-regulation
Other activities	Covers information regarding what is physical activity, exercise, and physical fitness. Further information regarding non-conventional activities and exercises.	Tailored information provided around methods of getting in “other” types of activities within their daily lives.	● Knowledge ● Optimism ● Self-efficacy ● Intentions
Health lifestyles	Provide informative content, both generally and lung cancer specific regarding lifestyle factors which may increase health-related quality of life.	Tailored information based on treatment type and lifestyle habits (smoking, alcohol, sleep, activity minutes), and personal values	● Knowledge ● Optimism ● Self-efficacy ● Intentions ● Motivation ● Beliefs about consequences
Breathlessness	Provide foundational information of what is breathlessness, causes, and exercises to help (both video and written demonstrations).	No tailoring	● Knowledge ● Self-efficacy
Mental health	Provides an introduction to mental health and lung cancer. Additionally, this module provides multiple links to external sources which discuss lung cancer and mental health-related factors.	No tailoring	● Knowledge ● Signage and support

#### Exercise prescription

The exercise prescription covers 8 weeks of tailored exercise. The adaptions to strength training are generally evident in individuals after 8 weeks [53, 54]. However, some studies highlight an increase in muscle cross-sectional area and strength after 2 to 4 weeks [55–57], likely due to neurological or connective tissue adaptations. Furthermore, 8 weeks of aerobic exercise has been illustrated to significantly improve aerobic capacity among those LWBLC [58].

The exercise prescription has been divided into two main categories: resistance-based exercise and aerobic-based exercise. Both components of exercise are based on participant-provided information. Exercise repetitions (reps) and sets are provided for the weekly programmes. Upon cessation of the week 1 to 3 exercise modules, participants will be asked to reflect on weeks 1 to 3 retrospectively. If too challenging, the frequency and intensity will be reduced. If the participants report the programme as appropriate, the programme frequency and intensity will slightly increase throughout weeks 4 to 8. Finally, if the participants report that the exercise programme was too easy, a larger increase in frequency and intensity will occur. Exercise safety information is provided in the exercise programme, prior to exercise prescription, and as a standalone safety module.

Participants will receive a minimum of two tele-coaching sessions at the beginning of weeks 1 and 4 to review the exercise prescription, safety queries, and any questions. Activities will be prescribed based on questions surrounding physical limitations, pain, and exercise experience.

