**Fig. 9 Fig9:**
[figure not shown]
Demonstrating the visual pain rating tool for resistance training exercises on ExerciseGuide UK

The frequency of resistance exercises will be 2 days per week for weeks 1 to 3, with eight to 12 reps maximum for two sets. At the end of week 3, the participants will be asked about their experience of the first 3 weeks. If the programme is perceived as “too hard”, the exercise will maintain at a stable level with possible modification throughout. The dose will remain two sessions per week, with two sets and eight to 12 reps for week 4. The participants will be informed to maintain this dose throughout, though at weeks 5 to 8, and they can increase to three sets of any exercise if they feel able.

In contrast, participants who rate the programme easy will be provided with three sessions per week for the remaining 4 weeks with an increased dose of three sets and 8–12 reps. Those who found the programme mildly challenging but achievable will be prescribed 2 days per week for weeks 4 and 5 and 3 days per week for weeks 6, 7, and 8, with reps ranging from 8 to 12. The Borg scale (see Fig. 8) will be used to illustrate the level of perceived exertion for resistance training. The PPI group recommend this scale, limiting the information and scales provided. Moreover, Natio and colleagues (2019) reported the one to ten Borg Scale was useful for elderly non-small cell lung cancer and pancreatic cancer patients performing resistance training [60]. The participants were informed to work at five–eight of their rate of perceived exertion.

The participants engaging in exercise sessions prior to participation in the study will be encouraged to continue their exercise but complete the prescribed exercises from ExerciseGuide UK. The participants will be encouraged by the exercise professional to engage in their own exercise regime in addition to ExerciseGuide UK if feasible.

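### The week-3 progression rules conflict in two places: whether frequency falls for participants who find the programme too hard, and whether the easy tier runs for four or five weeks

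*Protocol article*

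**What the plan says.** The article fixes the calendar in three places. The Exercise prescription section states "The exercise prescription covers 8 weeks of tailored exercise". Table 2, under Website tailoring, splits the programme in two and states "Section two will cover week 4 to week 8". The Resistance exercise section places the decision point: "At the end of week 3, the participants will be asked about their experience of the first 3 weeks".

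The starting dose is in the Resistance exercise section: "The frequency of resistance exercises will be 2 days per week for weeks 1 to 3", with two sets of 8 to 12 repetitions.

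The rule for participants who struggled appears twice:

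- Exercise prescription section: "If too challenging, the frequency and intensity will be reduced".
- Resistance exercise section: "the exercise will maintain at a stable level with possible modification throughout", followed by "The dose will remain two sessions per week, with two sets and eight to 12 reps for week 4". Participants are told to keep to this dose, with an optional third set in weeks 5 to 8.

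For those who found the programme easy, the Resistance exercise section prescribes "three sessions per week for the remaining 4 weeks", with three sets. The Exercise prescription section says this group receives the larger increase. The middle tier has two days per week in weeks 4 and 5 and three in weeks 6, 7 and 8.

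The Quantitative data section says that the weekly tracking module will be used to examine adherence to the prescription.

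**The concern.** These are stated dosing rules of the intervention under test, and the website applies its tailoring through automated IF-THEN statements. For a given answer at week 3, such a rule needs one defined output. The article gives two for the too-hard tier, and for the easy tier a duration that does not fit its own calendar.

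Two things are at stake. First, adherence is examined against the prescription, so it must be clear what was prescribed to each tier in each week. Second, the article is published partly to aid replication, and a reader cannot rebuild the progression for these two tiers from the text. The first conflict also concerns participants who have just reported that the programme is too hard, so the intended rule should be unambiguous.

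**Working it through.** No power or sample-size formula applies. The check is a comparison of the rules and a count of weeks and sessions.

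**Inputs.** Programme length 8 weeks (Exercise prescription); decision at the end of week 3 and tier doses (Resistance exercise); second section running from week 4 to week 8 (Table 2).

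**Too-hard tier.**

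- Sessions per week: 2 in weeks 1 to 3 and 2 afterwards. The change is 2 − 2 = 0, where the Exercise prescription section states a reduction.
- Weekly sets per exercise (sessions × sets): 2 × 2 = 4 in weeks 1 to 3; 2 × 2 = 4 in week 4; from 2 × 2 = 4 up to 2 × 3 = 6 in weeks 5 to 8.

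On the stated figures of the Resistance exercise section, neither sessions nor sets fall. The allowance for modification could cover some easing of intensity, but not the stated cut in frequency, because the frequency is given as a number and that number is unchanged.

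**Weeks left after the decision.** The plan's figure for the easy tier is 4. From its own calendar: 8 − 3 = 5 (weeks 4, 5, 6, 7 and 8). The figure of 4 can be reproduced only by counting weeks 5 to 8, and the easy tier then has no stated dose in week 4. The middle tier, in the same paragraph, is laid out over all five weeks.

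**Resistance sessions after week 3.**

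| Tier and reading | Calculation | Sessions |
|---|---|---|
| Too hard, Resistance exercise section | 5 × 2 | 10 |
| Too hard, Exercise prescription section | reduced, amount not stated | fewer than 10 |
| Middle | 2 × 2 + 3 × 3 | 13 |
| Easy, as written, week 4 unassigned | 4 × 3 | 12 |
| Easy, week 4 assumed to hold two sessions | 2 + 4 × 3 | 14 |
| Easy, three sessions in all five weeks | 5 × 3 | 15 |

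As written, the easy tier has fewer specified sessions than the middle tier (12 against 13), although it is meant to receive the larger increase.

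**Whole programme, easy tier.** Adding 3 × 2 = 6 sessions for weeks 1 to 3 gives 18, 20 or 21. Relative to 21, the gap is (21 − 20)/21 = 4.8% if week 4 holds two sessions, and (21 − 18)/21 = 14.3% if it holds none. The table shows the range only; it does not indicate which rule is right.

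**The case against.** The best defence is that the Exercise prescription section is a short overview of resistance and aerobic exercise together, while the Resistance exercise section gives the operative detail. On that reading the detail governs and the overview is loosely worded. This explains how the conflict could have arisen but does not remove it: resistance exercise is one of the two components the overview names, and the overview states a cut in frequency that the detail does not contain.

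Several stronger readings are tempting, and the document does not support them.

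- **The middle tier conflicts too.** A reader might set the promised slight increase across weeks 4 to 8 against two days per week in weeks 4 and 5. But a step from two to three days within that block is such an increase, and the overview does not say that it starts in week 4.
- **The easy-tier prescription is uncertain by 14%.** That requires no sessions at all in week 4 for people who found the programme easy. Nothing suggests this, and both other tiers have two sessions in week 4 under the Resistance exercise section.
- **The adherence denominator is undefined, so a feasibility result fails.** The article states no session-based ratio for adherence, and adherence is not among the pre-established criteria. Retention is defined by completing 80% of the intervention, but the article does not say that this is counted in sessions.
- **Participants who struggle are exposed to an unsafe escalation.** The third set is optional, modification is allowed, and the Exercise prescription and Virtual meeting sections provide for a contact at the start of week 4 at which a researcher goes through the prescription and checks its safety for the participant. That contact limits the concern, though it does not say which rule applies.
- **Two conflicting rules are running on the site.** The programmed algorithm is not shown. The text establishes inconsistent statements, not a fault in delivery.

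**Conclusion.** Two contradictions stand. The too-hard tier is stated to have its frequency reduced in one section and held at two sessions per week in another. The easy tier is given four weeks where the plan's calendar leaves five, so either the count is wrong or week 4 has no stated dose.

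The prescription is therefore unclear for two of three tiers. For the easy tier the range after week 3 is 12 to 15 sessions, or 14 to 15 on the assumption that week 4 holds two. For the too-hard tier the size cannot be given, because the amount of the reduction is not stated. All counts cover resistance sessions only.

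This should be fixed before adherence is analysed. It does not bear on the recruitment, usability, satisfaction or interview criteria, and it would bear on retention only if completion of the intervention were counted in sessions.

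**What to change.** The clinical and exercise team should reconcile Table 2, the Exercise prescription section and the Resistance exercise section into a single table with one row per tier and one column per week, giving sessions, sets and repetitions, including week 4 of the easy tier. They should check that table against the algorithm programmed in the website, correct whichever statement does not match the intended rule, and name the table as the reference for adherence. This review takes no position on which rule or dose is right.

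The cost is a correction to the text and a check of the live algorithm. No added data collection is needed.

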##### Resistance exercise

There are twenty-two possible resistance exercises that can be included in the exercise prescription. The computer-tailored website allows tailoring the exercise prescription based on physical activity and exercise experience, current physical activity and exercise levels, and overall and specific limits to physical health and activities of daily living. A list of the exercises is provided in supplementary material 1. An animation demonstration and written instruction will accompany each exercise (see Figs. 6 and 7).

**Fig. 6 Fig6:**
[figure not shown]
Stills of the animation (via embedded graphic interchange format (GIF) files) of the standing dumbbell row

**Fig. 7 Fig7:**
[figure not shown]
Example of the extra information provided to the participants for the standing bumbbell row

The intensity of the resistance exercises will be prescribed with a visual aid tool. In addition, the Rate of Perceived Exertion scale (see Fig. 8) and pain scale (see Fig. 9) will be provided to conceptualise perceived scoring. Participants are informed about aiming for the green zone of moderate activity for the exercises. Information to try contextualising the moderate activity zone will be provided in lay language. For example, referring to body heat and the ability to “talk and not sing,” contextual comparisons which PPI members felt were valuable and understandable.

**Fig. 8 Fig8:**
[figure not shown]
Rate of perceived exertion (RPE) used on ExerciseGuide UK adapted from Borg (1982) [59]

**Fig. 9 Fig9:**
[figure not shown]
Demonstrating the visual pain rating tool for resistance training exercises on ExerciseGuide UK

The frequency of resistance exercises will be 2 days per week for weeks 1 to 3, with eight to 12 reps maximum for two sets. At the end of week 3, the participants will be asked about their experience of the first 3 weeks. If the programme is perceived as “too hard”, the exercise will maintain at a stable level with possible modification throughout. The dose will remain two sessions per week, with two sets and eight to 12 reps for week 4. The participants will be informed to maintain this dose throughout, though at weeks 5 to 8, and they can increase to three sets of any exercise if they feel able.

In contrast, participants who rate the programme easy will be provided with three sessions per week for the remaining 4 weeks with an increased dose of three sets and 8–12 reps. Those who found the programme mildly challenging but achievable will be prescribed 2 days per week for weeks 4 and 5 and 3 days per week for weeks 6, 7, and 8, with reps ranging from 8 to 12. The Borg scale (see Fig. 8) will be used to illustrate the level of perceived exertion for resistance training. The PPI group recommend this scale, limiting the information and scales provided. Moreover, Natio and colleagues (2019) reported the one to ten Borg Scale was useful for elderly non-small cell lung cancer and pancreatic cancer patients performing resistance training [60]. The participants were informed to work at five–eight of their rate of perceived exertion.

The participants engaging in exercise sessions prior to participation in the study will be encouraged to continue their exercise but complete the prescribed exercises from ExerciseGuide UK. The participants will be encouraged by the exercise professional to engage in their own exercise regime in addition to ExerciseGuide UK if feasible.

